### Intervention

Eligible patients will receive oral pyrotinib 400 mg once daily and oral thalidomide 200 mg once daily until disease progression, intolerable toxicity, withdrawal of consent, or other reasons judged by the investigator. Dose adjustment, interruption, or discontinuation of study drug according to the adverse events (AEs) is detailed in Table 2.

**Table 2 Tab2:** Dose adjustment criteria

NCI CTCAE 5.0	Management (after active treatment and observation)	Dose adjustment after the study drug is continued
**Pyrotinib**		
Clinically significant grade ≥ 2 declined LVEF or LVEF lower than the lower limit of normal (including LVEF declining ≥10% and LVEF < 50% without symptoms, or heart failure)	Discontinue pyrotinib	
Grade 4 diarrhea	Discontinue pyrotinib	
Grade 3 diarrhea or grade 1–2 diarrhea with concomitant symptoms (including but not limited to mild to severe abdominal cramps, grade ≥ 2 nausea or vomiting, declined ECOG performance status, fever, pyemia, decreased neutrophil count, bleeding or dehydration)	Interrupt pyrotinib until diarrhea is restored to grade 0–1 and concomitant symptoms disappear	80 mg reduction each time to the minimum dose of 240 mg
Grade ≥ 2 non-hematologic AEs (except for alopecia, fatigue and asthenia)	Interrupt pyrotinib until diarrhea is restored to grade 0–1	80 mg reduction each time to the minimum dose of 240 mg
Grade ≥ 3 hematologic AEs	Interrupt pyrotinib until diarrhea is restored to grade 0–1	80 mg reduction each time to the minimum dose of 240 mg

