Pyrotinib is an oral, irreversible epidermal growth factor receptor (EGFR)/HER2 dual TKI. The combination of pyrotinib with capecitabine has been approved for the treatment of patients with *HER2*-positive, relapsed or metastatic breast cancer who were previously treated with taxanes, anthracyclines, and/or trastuzumab in China [14]. In a *HER2* exon 20 insertion patient-derived xenografts model, a more profound tumor regression was observed with pyrotinib than with afatinib and T-DM1 [15]. Two phase II trials have demonstrated the promising antitumor activity and acceptable safety profile of pyrotinib monotherapy in patients with previously treated, *HER2*-mutant advanced NSCLC, with the ORR of 53% (8/15) and 30% (18/60), and median PFS of 6.4 and 6.9 months, respectively [15, 16]. A multicenter, randomized phase III trial (NCT04447118) has been started to compare the efficacy and safety of pyrotinib versus docetaxel in patients with advanced non-squamous NSCLC harboring *HER2* exon 20 mutations who failed platinum-based chemotherapy. However, pyrotinib-related diarrhea remains an issue, with the incidence of 27% (4/15) and 92% (55/60) in previous phase II trials [15, 16]. Thus, we wanted to explore a combination regimen to further enhance the antitumor activity and improve the safety and tolerability of pyrotinib in advanced NSCLC patients with *HER2* exon 20 insertions.

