**Thalidomide**		
Constipation, somnolence, or peripheral neuropathy	Consider interrupting thalidomide	Dose can be reduced as per investigator’s discretion
Grade 3–4 AEs or clinically significant symptoms	Consider interrupting or discontinuing thalidomide	Dose reduction can be considered
Angioedema, allergic reaction, grade 4 rash, skin peeling, bullae, or any other severe skin reaction	Discontinue thalidomide	

*NCI CTCAE* National Cancer Institute Common Terminology Criteria for Adverse Events, *LVEF* left ventricular ejection fraction, *ECOG* Eastern Cooperative Oncology Group, *AE* adverse event

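### Table 2 ties pyrotinib restart to recovery of diarrhea after hematologic AEs and after non-hematologic AEs other than diarrhea, not to recovery of the AE that caused the interruption

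*Protocol article*

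**What the plan says.** The Intervention section sends the reader to one place for these rules: "Dose adjustment, interruption, or discontinuation of study drug according to the adverse events (AEs) is detailed in Table 2". The middle column of that table, which holds the instruction, is headed "Management (after active treatment and observation" (closing bracket omitted here).

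The pyrotinib part of Table 2 has five rows. Two stop the drug for good (LVEF decline and grade 4 diarrhea). Three interrupt it and then reduce the dose:

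- Grade 3 diarrhea, or grade 1–2 diarrhea with accompanying symptoms. Pyrotinib is held until the diarrhea is grade 0–1 and the accompanying symptoms have gone.
- "Grade ≥ 2 non-hematologic AEs (except for alopecia, fatigue and asthenia" (closing bracket omitted here). The instruction is "Interrupt pyrotinib until diarrhea is restored to grade 0–1".
- "Grade ≥ 3 hematologic AEs". The instruction is the same: "Interrupt pyrotinib until diarrhea is restored to grade 0–1".

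All three carry the same dose step on restart: "80 mg reduction each time to the minimum dose of 240 mg".

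**The concern.** A restart condition should name the event that caused the interruption. In the last two rows it names diarrhea whatever the event was. Read literally, a patient with a grade 3–4 cytopenia and no diarrhea already satisfies the condition when pyrotinib is stopped, while the cytopenia is still present. The same holds for a non-hematologic AE of grade 2 or higher that is not diarrhea.

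This is a dosing-safety rule for a two-drug combination, and the Discussion says the trial must stay alert to unexpected safety signals. The Background also hypothesizes that thalidomide will reduce diarrhea. If it does, a condition that asks only about diarrhea will restrain restart less often. Restart is at a lower dose, which limits the exposure but is no substitute for recovery.

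**Working it through.** No sample size, power or event figure is involved, so the check compares each row's trigger with its restart condition.

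**Row by row (Table 2, pyrotinib)**

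1. LVEF decline: discontinue. No restart condition is needed.
2. Grade 4 diarrhea: discontinue. No restart condition is needed.
3. Grade 3 diarrhea, or grade 1–2 with accompanying symptoms: restart when diarrhea is grade 0–1 and the symptoms are gone. Trigger and condition match.
4. Grade ≥2 non-hematologic AE, with three named exceptions: restart when diarrhea is grade 0–1. Grade 4 diarrhea, grade 3 diarrhea and grade 2 diarrhea with symptoms have their own rows. The diarrhea left for this row is therefore grade 2 without symptoms, and for that event the condition is right. It does not fit any other AE in the row.
5. Grade ≥3 hematologic AE: restart when diarrhea is grade 0–1. Diarrhea is not a hematologic AE, so the condition fits no event in the row.

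Count: 5 rows = 2 discontinue + 3 interrupt and reduce. Of those 3, one matches, one matches in part and one does not match.

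**Against the row above.** The diarrhea row lists a fall in neutrophil count, and nausea or vomiting of grade 2 or higher, among the accompanying symptoms that must disappear before restart. Taken literally, the table requires a neutrophil fall to resolve when it comes with grade 1–2 diarrhea, but does not require an isolated grade 3–4 neutropenia to resolve. It treats grade 2 vomiting in the same uneven way. It is hard to see a clinical reason for that. The shared wording in adjacent rows points strongly to text carried down from the diarrhea row, although the cause remains an inference.

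**Elsewhere in the article.** I looked for anything that would supply the missing condition:

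- The column heading places the action after active treatment and observation, but gives no recovery grade.
- The thalidomide row for grade 3–4 AEs ("Consider interrupting or discontinuing thalidomide") governs the other drug and gives no recovery grade either.
- The Intervention text ends treatment for intolerable toxicity or on the investigator's judgment. That is a stopping rule, not a restart rule.
- The Discussion mentions dose adjustment and interruption for diarrhea only as a threat to efficacy.

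**Dose on restart.** From the 400 mg starting dose, the steps are 400 − 80 = 320 mg and 320 − 80 = 240 mg, the minimum. A first restart is therefore at 320 mg.

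**The case against.** The best case against the point is that no one would follow the literal wording. Something can be restored to grade 0–1 only if it had worsened, and an interruption that ends as it begins would make the row pointless. A clinician would read the cell as meaning the triggering AE, and grade 0–1 is the only recovery grade printed in any interruption row. The column heading implies active management first, the diarrhea row already handles some cytopenias and vomiting that accompany diarrhea, and the investigator can stop treatment at any time. The article also condenses a full protocol that may have the correct text.

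Much of this stands, and it lowers the practical risk. It does not remove the defect. The safeguards listed do not cover a patient with an isolated cytopenia and no diarrhea. Nor is this a detail left to the full protocol, because the article does print a restart rule and the rule names the wrong event. A safety instruction should not depend on the reader noticing that it is wrong.

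The objection also limits the extent. A reader might infer that both cells are wrong throughout. The non-hematologic row is correct for isolated grade 2 diarrhea, so it is too narrow rather than wholly wrong. Only the hematologic row fits none of its triggers.

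**Conclusion.** The point holds as an error of wording in a dosing-safety rule. The hematologic row is wrong for every event it covers, and the non-hematologic row is wrong for every event except diarrhea. Neither requires the triggering toxicity to recover before pyrotinib resumes at the reduced dose, and the article does not say so anywhere else. It should be corrected. It has no bearing on the Simon two-stage design, the decision boundaries or the ORR analysis.

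A reader might go further in two ways that the document does not support.

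One is to put a number on the patients exposed. The Background reports pyrotinib-related diarrhea "with the incidence of 27% (4/15) and 92% (55/60) in previous phase II trials". The complements are 11/15 = 73% and 5/60 = 8%; scaled to 39 patients, 39 × 11/15 = 28.6 and 39 × 5/60 = 3.25. This range of about 3 to 29 should not be used:

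- It counts patients without diarrhea, not patients with a triggering AE.
- The article describes only the 55/60 as diarrhea of any grade (in the Discussion); it does not give the grade basis of the 4/15.
- Both rates come from monotherapy, while the combination is expected to change them.

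The article gives no rate of the triggering AEs under the combination, so the number affected cannot be estimated.

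The other is to conclude that patients are in fact being restarted during unresolved toxicity. That would require the operative protocol to carry the same wording and the site to apply it literally. Neither is known.

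**What to change.** In both cells, replace diarrhea with the triggering AE, so that the condition reads: *until the triggering AE is restored to grade 0–1*. The clinical team should confirm that grade 0–1 is the intended recovery level for hematologic AEs, since the article gives no separate one.

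Then check the operative protocol for the same wording. If it is there, correct it and send a clarification to the site; if it is not, a correction to the article is enough.

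The cost is two table cells and at most one clarification to a single center. Sample size, decision boundaries and timelines do not change.

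### In two pyrotinib rows of Table 2, the restart criterion names diarrhea instead of the adverse event that caused the interruption

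*Protocol article*

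**What the plan says.** The Intervention section of the protocol article refers to Table 2 for adjusting, interrupting or stopping study drug because of AEs, so Table 2 is the working rule set in this document. Its pyrotinib part has five rows.

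- Two rows end treatment: a row on left ventricular ejection fraction, covering "declined LVEF or LVEF lower than the lower limit of normal", and a row for "Grade 4 diarrhea".
- One row, triggered by "Grade 3 diarrhea or grade 1–2 diarrhea with concomitant symptoms", says "Interrupt pyrotinib until diarrhea is restored to grade 0–1 and concomitant symptoms disappear".
- One general row is triggered by "Grade ≥ 2 non-hematologic AEs (except for alopecia, fatigue and asthenia" and says "Interrupt pyrotinib until diarrhea is restored to grade 0–1".
- One row is triggered by "Grade ≥ 3 hematologic AEs" and repeats that same instruction.

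All three interruption rows give the same adjustment on restart: "80 mg reduction each time to the minimum dose of 240 mg". The starting dose is 400 mg once daily.

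**The concern.** An interruption rule needs an end point tied to its cause. In the general and hematologic rows the end point is the grade of diarrhea, which for most possible triggers is unrelated to why the drug was stopped. Taken literally, a patient interrupted for a severe hematologic AE could restart as soon as diarrhea is absent, whatever the blood count shows.

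This is a safety matter, because it governs when a drug held for toxicity may be given again. The article also adds thalidomide partly to suppress diarrhea. The better that works, the more often the printed criterion is met without saying anything about recovery.

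**Working it through.** There is no figure to reproduce. The check sets the five pyrotinib rows of Table 2 side by side and asks whether each restart condition refers to the row's own trigger.

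| Row (trigger, paraphrased) | Action | Restart condition | Refers to own trigger? |
|---|---|---|---|
| Ejection fraction decline | Stop | None needed | Not applicable |
| Diarrhea, grade 4 | Stop | None needed | Not applicable |
| Diarrhea, grade 3, or lower grade with accompanying symptoms | Interrupt | Diarrhea at grade 0–1 and symptoms gone | Yes |
| Non-hematologic AE, grade 2 or higher, three exceptions | Interrupt | Diarrhea at grade 0–1 | Only if the AE happens to be diarrhea |
| Hematologic AE, grade 3 or higher | Interrupt | Diarrhea at grade 0–1 | No |

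So 2 of the 3 interruption rows have a restart condition that does not name their trigger.

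**Test case.** Take a patient on 400 mg with a grade 3 hematologic AE and no diarrhea.

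1. The hematologic row applies, and pyrotinib is interrupted.
2. The restart condition asks for diarrhea of grade 0–1. Absent diarrhea satisfies it on the first day, and so would grade 1 diarrhea.
3. Restart is at 400 − 80 = 320 mg, which is 320/400 = 80% of the starting dose.
4. If the AE is still grade 3, the row applies again. The next restart is at 320 − 80 = 240 mg, which is 240/400 = 60% and the stated minimum.
5. The number of reductions available is (400 − 240)/80 = 2. One unresolved AE could use both.

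The same sequence holds for a grade 2 or higher non-hematologic AE other than diarrhea and the three exceptions.

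**Is it cured elsewhere?** The management column header says that the actions follow active treatment and observation, but it gives no recovery grade. No other part of the article supplies one. Chronic diarrhea is an exclusion (Table 1, exclusion criterion 3), so a patient without diarrhea when another AE occurs is an ordinary case. The instruction is a complete sentence, printed identically in both rows, so it does not look like a fault of text extraction.

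**How many patients?** This would need the rates of grade 2 or higher non-diarrhea AEs and of grade 3 or higher hematologic AEs. The article gives neither, so the count cannot be narrowed within 0 to 39.

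**The case against.** The strongest reply is that the table, read as a whole, does not license dosing through an unresolved AE. If pyrotinib restarts while the AE still meets its trigger, the row fires again and orders another interruption. In the non-hematologic row the trigger is grade 2 or higher, so it stops firing only at grade 0–1, very likely the intended restart level. The column header also points to treating the AE first, and any experienced investigator would wait for recovery.

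This softens the harm but does not remove the error. The criterion is still met at once by a patient without diarrhea, and each repeat trigger uses one of only two dose steps. In the hematologic row the trigger stops firing at grade 2, so repeat triggering does not reproduce a grade 0–1 recovery level, and no other level is printed.

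A reader might go further and infer that the rows contradict one another, since the general row excepts neither diarrhea nor ejection fraction decline. The text does not support much of this:

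- For grade 4 diarrhea and ejection fraction decline, the dedicated rows say stop. Reading the specific row over the general one is the ordinary approach.
- For grade 2 diarrhea without accompanying symptoms, the general row gives a determinate rule: interrupt to grade 0–1, then reduce. No row says to continue dosing. The symptom qualifier in the diarrhea row still has work to do for grade 1 and for the restart condition.

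It would also be wrong to estimate affected patients from the diarrhea rates of the two earlier pyrotinib trials (4/15 and 55/60). Those describe who had diarrhea on monotherapy. They do not describe who would be interrupted under these two rows.

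**Conclusion.** The error stands on the printed text: two of the three interruption rows let restart depend on diarrhea when the cause may be something else. It covers non-hematologic AEs of grade 2 or higher, apart from alopecia, fatigue and asthenia, and hematologic AEs of grade 3 or higher. It does not extend to every AE.

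The importance is minor. The wording is probably carried over from the diarrhea row, and investigators would probably wait for recovery. A reader might infer that patients were in fact restarted too early or that the efficacy result is at risk. The article shows neither, and the sample size and the response-rate decision rule do not depend on this wording. The conclusion assumes that Table 2 reflects the rules in use; the full protocol is not shown and may already be correct.

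**What to change.** Change two cells of the pyrotinib part of Table 2:

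- Non-hematologic row: interrupt pyrotinib until the AE that caused the interruption has recovered to grade 0–1.
- Hematologic row: the same wording, with grade 0–1 or whatever hematologic recovery grade the team intends, stated explicitly.

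Optionally, add to the non-hematologic row that AEs with a row of their own (diarrhea of grade 3–4 or with accompanying symptoms, and ejection fraction decline) follow that row. No new rule for uncomplicated grade 1–2 diarrhea is needed to correct this error; that would be a separate clinical choice.

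The cost is a wording correction and a note to the investigators at the single center, after checking the full protocol. If the full protocol is already correct, only the article needs correcting. Endpoints, sample size and primary analysis stay as they are.

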**Thalidomide**		
Constipation, somnolence, or peripheral neuropathy	Consider interrupting thalidomide	Dose can be reduced as per investigator’s discretion
Grade 3–4 AEs or clinically significant symptoms	Consider interrupting or discontinuing thalidomide	Dose reduction can be considered
Angioedema, allergic reaction, grade 4 rash, skin peeling, bullae, or any other severe skin reaction	Discontinue thalidomide	

*NCI CTCAE* National Cancer Institute Common Terminology Criteria for Adverse Events, *LVEF* left ventricular ejection fraction, *ECOG* Eastern Cooperative Oncology Group, *AE* adverse event

### Endpoints

The primary endpoint is ORR. The secondary endpoints are PFS, OS, disease control rate, safety, and patient-reported outcomes (European Organization for Research and Treatment of Cancer [EORTC] Quality of Life Questionnaire-Core 30 [QLQ-C30] and Quality of Life Questionnaire-Lung Cancer Module 13 [QLQ-LC13]) [29, 30].

Imaging examinations using computed tomography or magnetic resonance imaging will be conducted at baseline, 3 weeks, and every 6 weeks thereafter. Tumor response will be assessed according to the Response Evaluation Criteria In Solid Tumors, version 1.1 [27]. AEs during the treatment period and within 28 days after the last dose will be recorded and graded according to the National Cancer Institute Common Terminology Criteria for Adverse Events, version 5.0. Survival status will be followed by telephone every 3 months until death, lost to follow-up, or the termination of the study. Subsequent anti-cancer treatment after disease progression or discontinuation of the study treatment will be recorded.

### Statistical analysis

Simon’s two-stage minmax design was selected for sample size calculation. The combination therapy with pyrotinib and thalidomide will be ineffective or uninteresting if the ORR is lower than 30% and this regimen will be worthy of further study if the ORR is ≥50%. A total sample of at least 39 patients is expected to provide 80% power for the analysis at the significance level of 0.05, including 19 patients in the first stage and 20 patients in the second stage of the trial. If six or more patients respond at the completion of the first stage, the second stage can be conducted. Otherwise, the study will be terminated. If at least 16 of 39 patients show response, this combination therapy is effective and warrants further study.

Following intent-to-treat principle, the efficacy analyses will be performed in the full analysis set, defined as all patients who received at least one dose of study drug with at least one efficacy evaluation. Safety analyses will be performed in the safety set, defined as all patients who received at least one dose of study drug with at least one safety record. Descriptive statistics will be conducted on baseline characteristics, tumor response, patient-reported outcomes, and AEs. Survival curves will be plotted using Kaplan-Meier method. No data imputation will be performed for the missing data.

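### Both Simon two-stage cut-offs are one response too low for the stated minimax design, so the rule as written has a type I error of 9.0%, not 5%

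*Protocol article*

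**What the plan says.** The Endpoints section names objective response rate as the primary endpoint ("The primary endpoint is ORR"). The Statistical analysis section then fixes the whole design:

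- **Type:** a Simon "two-stage minmax design was selected for sample size calculation".
- **Rates:** the regimen "will be ineffective or uninteresting if the ORR is lower than 30" per cent, and "this regimen will be worthy of further study if the ORR is ≥50" per cent.
- **Size and error rates:** "A total sample of at least 39 patients is expected to provide 80% power for the analysis at the significance level of 0.05", split into 19 patients in stage 1 and 20 in stage 2.
- **Interim rule:** "If six or more patients respond at the completion of the first stage, the second stage can be conducted". With fewer responses the study ends.
- **Final rule:** "If at least 16 of 39 patients show response, this combination therapy is effective and warrants further study".

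No other section of the article gives a different rule or a different significance level.

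**The concern.** Simon designs are tabulated as r1/n1 and r/n, where r1 and r are the largest response counts at which the drug is rejected. Continuing needs r1 + 1 responses, and success needs r + 1. The article's 6 of 19 and 16 of 39 look like the tabulated r1 and r used directly as minimum counts for continuing and for success, which would put each boundary one response too low.

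This is the only prespecified success criterion for the primary endpoint. The null rate of 30% also equals the pyrotinib monotherapy ORR in the larger phase II trial cited in the Background (18/60). A final cut-off that is too low raises the chance of declaring the combination effective when it adds nothing to that rate. An interim cut-off that is too low sends more patients into stage 2 of an inactive regimen.

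**Working it through.** **Inputs**, all from the Statistical analysis section: p0 = 0.30, p1 = 0.50, alpha = 0.05, power = 0.80, n1 = 19, n2 = 20, n = 39. The section does not say whether 0.05 is one- or two-sided. It is taken as one-sided, the usual convention for this design.

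**Step 1. Reproduce the sample size.** An exhaustive exact-binomial search for the smallest n, then the smallest expected n under p0, gives r1/n1 = 6/19 and r/n = 16/39. The attained alpha is 0.0455 and the power 0.8036. The stage sizes match the article exactly, so the intended design is not in doubt. A one-sided 0.025 level would need n = 47, which confirms the one-sided reading of 0.05.

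**Step 2. Error rates of a rule.** For a rule that continues if X1 ≥ a1 and declares success if X1 + X2 ≥ a:

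P(success | p) = Σ over x = a1,…,19 of Bin(x; 19, p) × P(Bin(20, p) ≥ a − x)

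PET0 = P(Bin(19, 0.30) ≤ a1 − 1) is the probability of early termination under p0, and E0(N) = 19 + 20 × (1 − PET0).

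| Rule | Alpha (p = 0.30) | Power (p = 0.50) | PET0 | E0(N) |
|---|---|---|---|---|
| As written: ≥6/19, ≥16/39 | 0.0902 | 0.8889 | 0.474 | 29.5 |
| Minimax: ≥7/19, ≥17/39 | 0.0455 | 0.8036 | 0.666 | 25.7 |
| Final cut-off only: ≥6/19, ≥17/39 | 0.0488 | 0.8249 | 0.474 | 29.5 |
| Interim cut-off only: ≥7/19, ≥16/39 | 0.0810 | 0.8585 | 0.666 | 25.7 |

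For the written rule, E0(N) = 19 + 20 × (1 − 0.474) = 29.5. For the minimax rule it is 19 + 20 × (1 − 0.666) = 25.7.

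**Step 3. Which cut-off does the damage.** The total excess over the minimax design is 0.0902 − 0.0455 = 0.0447. Raising only the final cut-off removes 0.0902 − 0.0488 = 0.0414 of it. Raising the interim cut-off as well removes the remaining 0.0488 − 0.0455 = 0.0033. The interim error shows up mainly in early stopping: a regimen with a true ORR of 30% enters stage 2 with probability 1 − 0.474 = 0.526 instead of 1 − 0.666 = 0.334.

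**Step 4. Can another reading rescue the rule?**

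- *Interim stop ignored (single stage, ≥16/39):* alpha 0.0944, power 0.9002. This is worse.
- *Success kept at ≥16/39 with a stricter interim cut-off:* ≥7 gives alpha 0.0810. ≥8 gives 0.0638, with power already down to 0.787. ≥9 brings alpha to 0.041, but power is then 0.661. None meets both 0.05 and 80%.
- *Alpha 0.10 with 90% power:* this minimax design also has n = 39 and success at ≥16, but its first stage is 28 patients, and it contradicts the stated 0.05 and 80%.
- *0.05 read as two-sided:* the effective one-sided limit becomes 0.025, so the excess grows.

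**Step 5. The borderline result.** At 16/39 = 41.0%, the one-sided exact (Clopper-Pearson) 95% lower bound is 27.7%, below the 30% null. At 17/39 = 43.6% it is 30.0%. These bounds ignore the interim look and serve only as illustration.

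**The case against.** The arithmetic cannot be rebutted, but several points limit how far it reaches.

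- **The two cut-offs are not equally serious.** With six kept at the interim and 17 at the end, alpha (0.0488) and power (0.825) both meet the stated limits. The article promises no early-stopping probability and no expected sample size, and the maximum stays at 39. This stands: the final cut-off is the error that breaks the stated significance level. The interim cut-off is a departure from the named minimax design with a smaller cost.
- **The confidence bound is not a planned analysis.** Tumour response is to be summarised descriptively and no interval is named. This also stands. If such a bound were reported it would fall below the null at 16/39, but the finding does not depend on it.
- **The full protocol may be right and only the article wrong.** This is possible, and it is a reason to check that document first. It does not excuse the article, which states its rule in full, in unambiguous words, beside a significance level the rule does not meet.
- **The trial is under way.** The Study design section gives first recruitment in mid-2020 and stage 1 enrolment ending around December 2021, and the trial is open-label at one centre. Changing a success rule while responses are visible needs care. The change makes success harder, however, so it cannot be mistaken for favouring the regimen.

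It might also be said that 9% is tolerable in a phase II screen. That defence is not available, because the article itself states 0.05.

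**Conclusion.** The concern holds. The sample size is the correct minimax size, but its rejection boundaries have been used as minimum counts for continuing and for success. The written rule would declare a regimen with a true ORR of 30% effective with probability 0.090, almost twice the stated 0.05. Its power is 0.889 rather than the planned 80%. The chance of stopping such a regimen at stage 1 is 0.474 rather than 0.666.

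These figures assume a one-sided 0.05, a binding interim stop as the article words it, and exactly 19 and 39 evaluated patients. Neither relaxing the interim stop nor reading the level as two-sided helps the rule. This must be fixed before the final decision is made.

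**What to change.** First check the rule in the full protocol and the SAP, and bring all documents into line. Then state:

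- **Interim:** continue to stage 2 if at least 7 of 19 respond; stop at 6 or fewer.
- **Final:** regard the regimen as worth further study if at least 17 of 39 respond; reject it at 16 or fewer.
- **Error rates:** the 0.05 is one-sided; attained alpha 0.0455, power 80.4%.

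If stage 1 has already been decided at six or more, leave that decision and raise only the final cut-off to 17 of 39 (alpha 0.0488, power 82.5%).

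The cost is a short amendment and a correction to the published text. The amendment should be dated and recorded as the correction of a design error independent of the accruing data, and will presumably need ethics approval. No extra patients are needed. The success threshold rises by one response, and power falls from an unintended 89% to the planned 80–82%.

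### The primary efficacy set is called intent-to-treat but leaves out treated patients with no efficacy evaluation, which can only raise the reported ORR and leaves the 19- and 39-patient denominators unsecured

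*Protocol article*

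**What the plan says.** The primary endpoint is ORR (Endpoints). Under Statistical analysis the article states: "Following intent-to-treat principle, the efficacy analyses will be performed in the full analysis set". That set is "defined as all patients who received at least one dose of study drug with at least one efficacy evaluation". The section closes with "No data imputation will be performed for the missing data". Nothing in the article says that a treated patient without an evaluation counts as a non-responder, or whether such a patient is replaced.

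On timing, Endpoints says: "Imaging examinations using computed tomography or magnetic resonance imaging will be conducted at baseline, 3 weeks, and every 6 weeks thereafter". The earliest scheduled on-treatment look at the tumour is therefore week 3.

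The decision rule is given as counts on fixed numbers. The second stage opens with six or more responders among the first 19 patients, and the regimen is declared effective with 16 or more responders among 39. The sample size is described as a minimum: "A total sample of at least 39 patients is expected to provide 80% power for the analysis at the significance level of 0.05".

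**The concern.** Having an efficacy evaluation is something that happens, or fails to happen, after treatment starts. A set conditioned on it is not an intent-to-treat set, so the label and the definition contradict each other within one sentence. The patients at risk of exclusion are those who die, deteriorate, withdraw or stop for toxicity before the first evaluation. None of them can be a recorded responder, so each exclusion leaves the numerator alone and shrinks the denominator.

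This matters more than usual here. The trial has one arm and judges its result against a fixed 30% rate, so no control group shares the bias. Tolerability is also part of the rationale for the combination, and early toxicity failures are among the patients who would drop out of the estimate. Finally, the two-stage rule has known error rates only for 19 and 39 patients, and under this definition the number analysed may be neither.

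**Working it through.** **Inputs from the documents (Statistical analysis, Endpoints).** Design: "two-stage minmax design was selected for sample size calculation". Null rate p0 = 0.30, target rate p1 = 0.50, alpha 0.05, power 80%, stages 19 + 20 = 39. Written rule: continue with ≥6/19, success with ≥16/39. Sidedness is not stated; one-sided is assumed, as is usual for this design.

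**Input assumed.** The documents give no non-evaluable rate. I use d = 2.6% (about 1 in 39), 5%, 10% and 15%, and take every non-evaluable patient to be a non-responder.

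**Step 1: reproduce the plan's sample size.** With continuation cut-off c1 and final cut-off c,

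Pr(success | p) = Σ over x from c1 to 19 of Pr(Bin(19, p) = x) × Pr(Bin(20, p) ≥ c − x).

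An exact search for the minimax design returns 19 + 20 = 39, so the stated size reproduces. That design continues with ≥7/19 and succeeds with ≥17/39: alpha 0.0455, power 0.8036. The cut-offs as written (≥6/19, ≥16/39) give alpha 0.0902 and power 0.8889. They are each one too low, which is a separate error. The error rates below use ≥7/19 and ≥17/39 so that the two problems are not mixed.

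**Step 2: the estimate.** With R responders among N treated and m dropped, the reported ORR is R/(N − m), which is never below R/N. For R = 16 and N = 39:

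| Dropped | Reported ORR |
|---|---|
| 0 | 16/39 = 41.0% |
| 2 | 16/37 = 43.2% |
| 3 | 16/36 = 44.4% |
| 4 | 16/35 = 45.7% |

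**Step 3: the decision, 39 treated, none replaced, responders counted.** Dropping non-responders leaves R unchanged at both stages. The go/no-go outcome and the error rates are those of Step 1.

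**Step 4: the decision, non-evaluable patients replaced until 19 and 39 are evaluable.** A true ORR of 30% among treated patients appears in the set as 0.30/(1 − d). Putting that rate into the Step 1 formula with ≥7/19 and ≥17/39:

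| d | Apparent ORR | Type I error |
|---|---|---|
| 0 | 30.0% | 0.0455 |
| 2.6% | 0.30/0.974 = 30.8% | 0.057 |
| 5% | 0.30/0.95 = 31.6% | 0.071 |
| 10% | 0.30/0.90 = 33.3% | 0.109 |
| 15% | 0.30/0.85 = 35.3% | 0.165 |

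**Step 5: the decision, rule read as a proportion.** The written threshold is 16/39 = 41.0%. With three patients dropped, 15/36 = 41.7% passes, although the same 15 responders among 39 treated, 38.5%, would fail.

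**The case against.** A reader might infer that the definition breaks the two-stage rule outright and inflates type I error in every case. The documents do not support that. The rule is written as responder counts, the abstract speaks of 39 patients recruited, and no replacement policy appears anywhere. On that natural reading Step 3 applies and the decision is untouched. The mention of at least 39 patients leaves room for more, but it sets no replacement rule.

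Nor does the bias favour the regimen at the decision level in every scenario. If evaluability were unrelated to response, the count cut-offs were kept and only 36 patients were evaluable, power would fall from 0.804 to 0.681 with ≥7/19 and ≥17/39 (from 0.889 to 0.793 with the written cut-offs). The one-directional statement holds for the reported ORR, compared with counting every treated patient.

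Two further points stand. The term efficacy evaluation is not defined, so documented clinical progression or death might qualify, which would shrink the bias; the article does not say so. The number lost may also be small, given a first scan at week 3, performance status 0–1 and a required life expectancy of at least three months.

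What the objection does not remove is the contradiction. The primary set is stated, it is stated as intent-to-treat, and applied as written it excludes treated patients for a post-treatment reason. This is a stated rule, not detail left to a fuller document.

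**Conclusion.** The point holds for the estimate and conditionally for the decision. Applied as written, the set can drop early failures, and the reported ORR can then only be too high: by 44.4% − 41.0% = 3.4 percentage points with 16 responders and three exclusions. The 19- and 39-patient denominators are not guaranteed, and the article does not say how the rule applies when they are not met. Type I error is inflated only under replacement (0.057 to 0.109 for 2.6% to 10% non-evaluable, against 0.0455) or if the rule is read as a proportion. These figures rest on an assumed rate, on all non-evaluable patients being non-responders, and on the minimax cut-offs instead of the written ones.

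**What to change.** Define the primary ORR set as all patients who took at least one dose. State that anyone without an evaluable post-baseline assessment is a non-responder, at both the 19-patient and the 39-patient decision, and that such patients are not replaced. Word this as part of the response definition, so that it does not clash with the sentence ruling out imputation. Keep the current evaluable set as a sensitivity analysis, and describe it as evaluable patients, not as intent-to-treat.

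The denominators then stay at 19 and 39 and the design keeps its exact properties (alpha 0.0455 and power 0.8036 with ≥7/19 and ≥17/39). The written cut-offs need their own correction, which this change does not supply.

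The cost is a few lines of text and possibly a slightly lower reported ORR. The change should be made before the stage decisions are taken, because choosing the denominator afterwards would be data-driven.
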